# Guided Internet-Based Cognitive Behavioral Therapy for Women With Bulimia Nervosa: Protocol for a Multicenter Randomized Controlled Trial

**DOI:** 10.2196/49828

**Published:** 2023-09-19

**Keywords:** bulimia nervosa, internet-based cognitive behavioral therapy, ICBT, randomized controlled trial, RCT, protocol, randomized, controlled trial, bulimia, eating, cognitive behavioral therapy, CBT, binge eating, purging, mobile phone

## Abstract

**Background:**

Individual face-to-face cognitive behavioral therapy is known to be effective for bulimia nervosa (BN). Since foods vary considerably between regions and cultures in which patients live, cultural adaptation of the treatment program is particularly important in cognitive behavioral therapy for BN. Recently, an internet-based cognitive behavioral therapy (ICBT) program was developed for Japanese women with BN, adapted to the Japanese food culture. However, no previous randomized controlled trial has examined the effectiveness of ICBT.

**Objective:**

This paper presents a research protocol for strategies to examine the effects of guided ICBT.

**Methods:**

This study is designed as a multicenter, prospective, assessor-blinded randomized controlled trial. The treatment groups will be divided into treatment as usual (TAU) alone as the control group and ICBT combined with TAU as the intervention group. The primary outcome is the total of binge eating and purging behaviors assessed before and after treatment by an independent assessor. Secondary outcomes will include measures of eating disorder severity, depression, anxiety, quality of life, treatment satisfaction, and working alliances. Treatment satisfaction and working alliances will be measured post assessment only. Other measures will be assessed at baseline, post intervention, and follow-up, and the outcomes will be analyzed on an intention-to-treat basis.

**Results:**

This study will be conducted at 7 different medical institutions in Japan from August 2022 to October 2026. Recruitment of participants began on August 19, 2022, and recruitment is scheduled to continue until July 2024. The first participants were registered on September 8, 2022.

**Conclusions:**

This is the first multicenter randomized controlled trial in Japan comparing the effectiveness of ICBT and TAU in patients with BN.

**Trial Registration:**

University Hospital Medical Information Network UMIN000048732; https://center6.umin.ac.jp/cgi-open-bin/ctr_e/ctr_view.cgi?recptno=R000055522

**International Registered Report Identifier (IRRID):**

DERR1-10.2196/49828

## Introduction

### Background

Bulimia nervosa (BN) is an eating disorder characterized by binge eating, purging or fasting, and concerns associated with body shape and weight [1]. Patients with BN often have a distorted body image despite being at standard levels with regard to shape and weight [2]. Consequently, they perform frequent purging or fasting or excessive exercise on the basis of a subjectively abnormal perception of their body shape and weight [3]. Body image distortion involves perceptual disturbances and body dissatisfaction [4]. Repeated episodes of binge eating and inappropriate compensatory behaviors can cause serious physical and mental health concerns. Vomiting after overeating may result in thickened skin on the knuckles, broken teeth, and thyroid dysfunction due to problems with metabolic rate and caloric intake [5,6]. In terms of mental health, patients with BN frequently show low self-esteem, self-harming behaviors, suicidal tendencies, depression, anxiety disorders, sleep disorders, and fatigue or exhaustion [7-12].

### Prevalence of BN and Accessibility to the Treatment

Epidemiological studies confirm that eating disorders are highly prevalent, particularly among women: 2.58% of women in Western countries [13]. The overall observed prevalence of eating disorders was 3.5% between 2000 and 2006 and increased to 7.8% between 2013 and 2018 [14]. A recent meta-analysis estimated that the lifetime and 12-month prevalence of eating disorders was 0.91% and 0.43%, respectively, while the lifetime prevalence of BN was 0.63% [13]. Face-to-face cognitive behavioral therapy (CBT) has been shown to be effective for eating disorders [15], but poor access to treatment remains a problem [16]. In fact, only 19%-36% of people with eating disorders have access to treatment within 1 year [17-19], and 35%-40% of these patients receive standard treatment for eating disorders [20,21]. Furthermore, treatment for eating disorders is sought an average of 5-15 years after the onset of the disorder [16,22]. Access to these appropriate treatments is often hampered by physical barriers, lack of practitioners, and stigma. These problems are particularly associated with face-to-face delivery. Web-mediated interventions may be effective in initiating appropriate early treatment [23,24]. CBT via the internet can dramatically improve access to treatment, especially in developed countries, in which the internet infrastructure is well-developed and information communication devices are widely used.

### A New CBT Model for BN

Enhanced CBT has been shown to be effective in treating eating disorders, including BN. Enhanced CBT encourages the early establishment of healthy and safe eating habits and facilitates behavioral changes and cognitive modification through psychoeducation and self-monitoring. In addition, accumulating evidence from many clinical studies is being integrated to establish CBT techniques that have shown promise for the treatment of eating disorders. In a network analysis, fear of weight gain was suggested to be central to the psychopathology of BN, and hypersensitivity to physical sensations was shown to bridge BN with anxiety or depression [25]. Based on the evidence, this network meta-analysis argued that focusing on the fear of weight gain during exposure therapy and interventions focused on interoceptive exposure is effective in treating BN. However, several other CBTs may also be effective in treating BN, including attentional bias correction training to correct the direction of excessive attention to the body, weight, and food [26], relaxation, and mindfulness to reduce physiological responses such as anxiety and tension [27], traumatic memory care for experiences of being criticized for one’s body type and appearance [28], and impulse control, such as cue exposure [29]. A therapist’s manual for CBT of BN that systematically summarizes these CBT components has been published by [name] and [name] [30]. Our research group recently developed a web-based program based on this CBT therapist’s manual by checking the cultural adaptability in Japan [31].

### Objectives

As mentioned earlier, we developed an internet-based cognitive behavioral therapy (ICBT) program for BN that is adapted to Japanese culture and based on Japanese food culture [30,31]. This paper describes the study protocol for a randomized controlled trial (RCT) involving female patients with BN and is designed to evaluate its clinical effects. We will include an intervention group receiving ICBT in addition to treatment as usual (TAU) and a control group receiving TAU alone.

## Methods

### Study Design

This study is designed as a multicenter, prospective, randomized, assessor-blinded clinical trial. The RCT and follow-up study are planned from August 2022 to October 2026 (UMIN000048732). It will be conducted at the following 7 institutions (6 university hospitals and a national medical center) in Japan: University of Fukui Hospital, Kagoshima University Hospital, Chiba University Hospital, Tokushima University Hospital, Dokkyo Medical University, Tohoku University Hospital, and National Center for Neurology and Psychiatry.

### Participants and Eligibility Criteria

Eligible participants will be women aged 13-65 years (1) diagnosed with BN according to the Diagnostic and Statistical Manual of Mental Disorders criteria during a clinical interview [1]; (2) having a BMI over 17.5 kg/m^2^; (3) using computers, tablets, smartphones, etc, on a daily basis, with access to the internet and the minimum necessary information and communications technology skills; and (4) with no history of CBT in the last 2 years. Exclusion criteria include (1) serious mental disorders such as organic brain disorders, psychotic disorders, and drug dependence; (2) imminent risk of suicide; (3) repeated engagement in antisocial behavior; (4) serious progressive physical disease; and (5) difficulty in exposure to feared objects due to severe stress reactions or dissociation symptoms due to acute stress disorder or posttraumatic stress disorder. The purpose of the study is to investigate the effects of an ICBT program that has been adapted based on the culture of Japanese women. Men and women differ in their caloric needs, and most studies regarding eating disorders include female patients. This intervention program is based on the findings of previous studies; therefore, only women will be recruited. In addition, information and communication technology literacy varies considerably by patient age in Japan, with older adults having lower information and communication technology literacy. The intervention in this study is mainly self-help CBT using a web-based platform. Therefore, patients aged 65 years and older will be excluded from the study.

### Recruitment

From August 2022 to July 2024, we will recruit 60 out-participants with female BN through posters, flyers, web or app advertisements (Google Ads, Twitter, and Facebook), newspaper advertisements, etc, posted at medical institutions throughout Japan. Since all participants will continue to be treated, they will be required to obtain clearance from their primary care physician prior to their study enrollment. The participants pay for TAU, but guided ICBT is free. Participants will be rewarded US $82.51 after intervention or waiting completion, regardless of group allocation. These include the amount of time patients spent on the trial and the difficulty of recruiting patients. To participate in this study, some hospitals will require referrals, which may cost the participant money.

### Procedure

Participants will be directed to a website for this study by the various media mentioned earlier. There they will access the study website to apply for enrollment in the study. The clinical trial office at the University of Fukui that receives this application will coordinate the informed consent and eligibility test. Written informed consent will be solicited after the participants are provided research briefing either face-to-face or in a video call. Similarly, in the case of a minor, written informed consent from a legal representative is required. Next, they will complete a screening survey and a structured interview using Mini International Neuropsychiatric Interview version 5 [32,33]. Finally, they will be asked to complete a baseline data questionnaire on the web. The decision regarding the participant’s exclusion or inclusion in the study will be made after they have completed the questionnaire. See Figure 1 for the flow of participants in this RCT.

**Figure 1 figure1:**
[figure not shown]
Flowchart of the recruitment and assessments during this study. ICBT: internet-based cognitive behavioral therapy.

3	Metacognitive training	Metacognition, one of the cognitive functions, is vulnerable in eating disorders [36], and there is evidence that cognitive weakness affects QOL^d^ [37]. Metacognitive interventions may improve eating disorder severity, depression, and QOL [24,38]. This involves dichotomous thinking, emotional judgment, jumping to conclusions, and perfectionism, among others [30,31].
4	Attention bias modification and modification of interpretation for appearance	People with eating disorders tend to focus on body shape, weight, and food overload [39,40]. Exercises are provided that shift attention from food stimuli to neutral stimuli [41,42]. People with eating disorders frequently rate their body shape and weight negatively [43]. When recognizing the threatening bias of one’s natural body shape and weight, the client can use techniques of relaxation and metacognition to handle concerns about perceived body shape and weight.
5	Behavioral experiment for binge eating	Behavioral experiments will be used to see that eating does not lead to uncontrolled weight gain [44].
6	Management of healthy food contents and eating habits	Self-monitoring using food diaries reduces the frequency of binge eating in web-based programs [45]. We propose a Japanese food menu to achieve a well-balanced diet [31]. This approach was developed based on a nutritional rehabilitation called “mechanical diet” by Garner et al [46].
7	Creating an anxiety hierarchy chart and stepwise exposure	Addressing fears associated with overeating can reduce overeating in BN [47,48].
8	Exposure to cues preceding binge eating and purging	Triggers for overeating and purging vary from person to person; however, exposure to such cues can reduce overeating and purging [29].
9	Cognitive restructuring	Negative self-statements associated with eating disorders are frequently observed in BN [49]. Such self-assertions shape the person’s own identity and values [50]. Cognitive restructuring fosters alternative ways of thinking about these self-statements (adaptive thinking).
10	Rewriting of traumatic memory for image of the body	There are often individuals with BN who have negative childhood experiences [51]. If the interpretation of a traumatic memory is tormenting the patient, it should be rewritten to make it safer.
11	Schema work	Rescripting dysfunctional beliefs (schemas) may reduce the frequency of binge eating and purging as well as body shape concerns [52]. Dysfunctional beliefs are organized and alternative beliefs are written down.
12	Prevention of relapse	A summary of what participants have learned from the treatment will be solicited and used to plan future efforts to further reduce symptoms and prevent relapse.

^a^DSM-5: Diagnostic and Statistical Manual of Mental Disorders, Fifth Edition.

^b^BN: bulimia nervosa.

^c^CBT: cognitive behavioral therapy.

^d^QOL: quality of life.

#### TAU (Control Group)

Participants will be allowed to continue receiving counseling, psychotropics, and other medications for the duration of the study. No new drug therapy or additional changes will be recommended during the study period by the study staff. However, the participant’s primary care physician will not be prevented from modifying medications and refer participants to counseling or second-line therapy if deemed clinically appropriate. All changes in TAU will be documented along with the reasons for these changes. Participants in the control group (TAU) will be offered ICBT after a waiting period as well.

### Measures

#### Demographic Data

Participants will be asked about age, educational level, marital status, employment status, BMI, age at BN onset, duration of BN, comorbidities, and the presence or absence of psychotropic or antidepressant drug use.

#### Primary Outcome

The primary outcome will be the weekly combined frequency of binge eating and purging behaviors. These will be measured by an independent assessor whose allocations are masked.

#### Secondary Outcomes

Secondary self-reported outcomes will be the Eating Disorders Examination Questionnaire [53,54], Patient Health Questionnaire-9 [55,56], Generalized Anxiety Disorder Scale-7 [56,57], EQ-5D [58,59], Brunnsviken Brief Quality of Life Scale [60] at baseline, postintervention, and follow-up (1-, 3-, 6-, 9-, and 21-month follow-ups). Assessments based on the Working Alliance Inventory-Short Form [61] and Client Satisfaction Questionnaire [62,63] will be performed only after the treatment.

### Sample Size

The required sample size was calculated using statistical analysis software (G*Power, version 3.1; Heinrich-Heine-Universitaet Duesseldorf). An effect size of Cohen *d*=0.90 from a previous study was used as a reference [64]. The significance level was set at *P* values <.05 for 2-sided tests. The power was set to 80%. The required sample size (assigned number of participants) will be 60 when considering a 30% noncompletion rate based on a previous study [65]. Completers in this study are defined as those who complete at least 80% of the module [65]. In addition, dropouts in this study are defined as those who drop out by not providing postevaluation data or those who discontinue their participation due to adverse events.

### Randomization

Participants confirmed to be eligible and enrolled will be randomized in a 1:1 ratio to either the intervention (TAU added guided ICBT) or TAU alone groups by the truncated binomial design using UMIN’s (University Hospital Medical Information Network) computer program (UMIN Center). The truncated binomial design is that complete randomization will be performed until the number of randomizations to any group reaches n/2, after which all subjects are allocated to the other group to prevent an imbalance in the number of people.

### Statistical Analysis Plan

Statistical analysis will be performed using SPSS Statistics software (version 29; IBM Corp). Statistical analysis will be performed in accordance with the CONSORT (Consolidated Standards of Reporting Trials) guidelines and based on the intention-to-treat principle (Multimedia Appendix 1). Missing data will be handled by multiple imputations. Unpaired *t* test and Fisher exact test will be used to investigate the difference between the 2 groups at baseline. To compare treatment effects, we will use analysis of covariance for primary and all secondary outcomes. As a covariate, we plan to include a scale that is significantly different between the 2 groups at baseline. We also will perform a per-protocol analysis by excluding patients who deviate from the protocol. Analysis of covariance will also be performed on the follow-up data. However, if there are many missing values, we would consider generalized linear mixed models. All *P* values are 2-tailed, and *P* values <.05 will be considered statistically significant.

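### ANCOVA covariates are chosen by baseline significance tests, so the outcome's own baseline is left out of the model about 95% of the time

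*Protocol article*

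**What the plan says.** All of the relevant text is in the Statistical Analysis Plan section of the protocol article. The baseline comparison comes first: "Unpaired *t* test and Fisher exact test will be used to investigate the difference between the 2 groups at baseline". The analysis model follows: "To compare treatment effects, we will use analysis of covariance for primary and all secondary outcomes". The next sentence is the only one on covariates: "As a covariate, we plan to include a scale that is significantly different between the 2 groups at baseline". The threshold for all tests is given at the end of the section: "All *P* values are 2-tailed, and *P* values <.05 will be considered statistically significant". The same method carries over to later time points: "Analysis of covariance will also be performed on the follow-up data".

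The primary outcome is defined in the Primary Outcome section: "The primary outcome will be the weekly combined frequency of binge eating and purging behaviors". The abstract confirms that its baseline is collected: "The primary outcome is the total of binge eating and purging behaviors assessed before and after treatment by an independent assessor". No sentence commits to adjusting for that baseline value, or for the baseline of any secondary outcome, irrespective of the test result.

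**The concern.** A covariate earns its place in an ANCOVA by predicting the outcome. The P value of a baseline difference says nothing about that. In a randomised trial it tests a null hypothesis known to be true, so selecting on it picks up chance findings at the 5% rate.

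Three things follow.

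- The strongest likely predictor of post-treatment binge/purge frequency, its own baseline, is usually omitted. When no scale is significant, the planned ANCOVA has no covariate and is a plain two-group comparison.
- A sizeable but non-significant imbalance is not corrected. The Randomization section describes no stratification by baseline severity, so in a trial of 60 adjustment is the only stated safeguard.
- The model is not known until the baseline tests have been run, and the scale that enters may not be the baseline of the outcome being analysed.

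The rule governs the primary, all secondary and the follow-up analyses.

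**Working it through.** **Inputs from the article.** d=0.90, two-sided alpha 0.05, power 80%, 30% noncompletion and 60 participants (Sample Size section); 1:1 allocation (Randomization section); covariate rule at P<.05 (Statistical Analysis Plan section).

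**Assumptions.** The baseline-to-outcome correlation r is not given; 0.3, 0.5 and 0.7 are shown. Baseline and outcome are taken as bivariate normal, and the post-treatment score is the dependent variable.

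**1. Reproducing the planned sample size.** For a two-sample t test the noncentrality is d × √(n/2).

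- 21 per arm: 0.90 × √10.5 = 2.92, power 81.2%.
- 20 per arm: power 79.2%.

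So 42 analysed are needed, and 42 / (1 − 0.30) = 60. The stated figure reproduces as an unadjusted t test with no credit for a covariate.

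**2. How often the baseline enters.** By design a test at 0.05 of a true null is significant 5% of the time. In simulation (100,000 trials per setting) the outcome's own baseline entered in 4.8–5.1% of trials, so it was left out in about 95%.

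**3. Power at d=0.90, 21 per arm.**

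| r (assumed) | Plan's rule | Baseline always in model |
|---|---|---|
| 0.3 | 81.4% | 83.9% |
| 0.5 | 82.1% | 90.0% |
| 0.7 | 82.9% | 97.5% |

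If the true effect is smaller, d=0.50, the pairs are 35.2% vs 37.3%, 35.0% vs 43.7% and 35.5% vs 58.7%. At r=0.5 the SD of the effect estimate is 0.298 under the rule and 0.270 with fixed adjustment.

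Another way to see the gain: fixed adjustment multiplies the residual variance by 1 − r². For 80% power at d=0.90 it needs 38, 32 or 22 analysed participants at r=0.3, 0.5 or 0.7, against 42 unadjusted.

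**4. Imbalance the rule ignores.** The largest non-significant difference, in SD units, is t(0.975, 2n−2) × √(2/n).

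- 21 per arm: 2.021 × 0.3086 = 0.62 SD.
- 30 per arm: 2.002 × 0.2582 = 0.52 SD.

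An uncorrected imbalance moves the estimate by r times its size. At r=0.5 the ceiling is 0.5 × 0.62 = 0.31 SD or 0.5 × 0.52 = 0.26 SD. That is 0.31/0.90 = 34% or 0.26/0.90 = 29% of the planned effect. These are worst cases: among trials with a non-significant imbalance the median shift is about 0.10 SD (21 per arm) or 0.08 SD (30 per arm).

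**5. Type I error, 21 per arm.**

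| r (assumed) | All trials, plan's rule | Trials with a non-significant imbalance above 0.4 SD, plan's rule |
|---|---|---|
| 0.3 | 4.8% | 6.4% |
| 0.5 | 4.2% | 8.7% |
| 0.7 | 3.7% | 11.2% |

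The right-hand column applies to about 14.5% of trials. With fixed adjustment the rate is about 5% in both columns.

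**6. Uncertainty about the model.** Six scales are measured at baseline: the primary outcome and the five repeated questionnaires in the Secondary Outcomes section. If their tests were independent, at least one would be significant in 1 − 0.95⁶ = 26% of trials.

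**The case against.** The strongest reply is that nothing the protocol promised is broken. The sample size rests on an unadjusted t test, and power under the rule stays at 81–83% for the planned effect. What is forgone is a gain that the plan never counted on, and its size depends on an unknown r: about 2.5 points at r=0.3, 15 at r=0.7, and none if r is near zero. Averaged over randomisations the estimate is unbiased and the test is slightly conservative. All of this stands, and it lowers the urgency.

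Selection uses baseline data and a threshold set in advance, so the rule does not let the analyst choose a model by its result. That also stands. The fault is that the model is unpredictable and poorly chosen.

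It can further be said that ANCOVA silently includes the outcome's baseline and that the rule only adds covariates. In a condensed article this is possible, but the text does not say it: the sentence describes how the covariate is chosen, not an additional one. If that is the intent, the same sentence still needs rewriting.

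The dependent variable is not stated either. If change from baseline were analysed without a covariate, power with 21 per arm would be about 67%, 81% and 96% at r=0.3, 0.5 and 0.7. The gap to fixed adjustment then nearly closes at r=0.7 but widens at r=0.3. Fixed adjustment is ahead in all three cases.

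Finally, the simulations use normal data, whereas weekly event counts are probably skewed, and they do not model the planned multiple imputation. The power figures are therefore indicative.

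**Conclusion.** The point holds. The article states a covariate rule, and it is the wrong kind of rule, so this is not a detail left to a fuller plan. On the literal reading the baseline of the primary outcome is left out about 95% of the time. That figure follows from alpha alone and needs no assumption about r.

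The cost in power at d=0.90 with 42 analysed is about 2.5, 8 and 15 percentage points at r=0.3, 0.5 and 0.7, relative to always adjusting. It rests on the assumed r, normal data and the post score as the dependent variable. Chance imbalance short of significance goes uncorrected, with a worst-case shift of about a third of the planned effect at r=0.5 and a typical shift near a tenth (0.10/0.90 = 11%).

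Because planned power is met and overall type I error is not inflated, this should be fixed but does not by itself endanger the trial.

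**What to change.** Replace the covariate sentence in the Statistical Analysis Plan section with wording such as: *Every ANCOVA will include the baseline value of the outcome being analysed as a pre-specified covariate, whatever the size of the baseline difference.* Apply it to the primary, secondary and follow-up analyses. With the baseline in the model, analysing the post score or the change gives the same treatment estimate, so the question of the dependent variable is settled too.

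Report baseline characteristics descriptively, and drop the t and Fisher tests as a step in building the model.

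The cost is one sentence, amended before unblinding. It needs no extra data and no extra participants, and the sample size of 60 can stay as it is.
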